### Study setting

The CHIP intervention will be conducted by CHIP trained volunteers in selected community halls on the Central Coast of NSW. A demographic and lifestyle survey will be administered at the venue the intervention is conducted. Anthropometric measurements and blood collection will occur at the venue at which the CHIP intervention is being conducted unless the facility is not suited for medical data collection in which case it will be collected at selected general practices.

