### Allocation of participants to a study group

Invitees who are willing to participate will be recorded on a list until such time as there are between 30 and 40 individuals listed. At this point, the individual participants will be randomized into either Group 1 or Group 2.

Once allocated, participants in Group 1, will receive the CHIP intervention over a period of 12 weeks. At the end of the 12 weeks period, Group 1 will receive monthly follow-up for a further 9 month period. This process will be repeated, until the full number of participants have been collected and assigned.

An overview of the study design and allocation of participants is illustrated in Fig. 1.

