### Interventions

#### Group 1- intervention group

All participants in Group 1 will participate in the CHIP intervention for 12 weeks. The CHIP intervention consists of 18 education sessions, each of 90 min duration. Approximately half of each session is devoted to viewing pre-recorded visual material delivered by lifestyle medicine professionals, while interactive group discussions and activities, including food preparation and exercise demonstrations delivered by CHIP trained volunteers, make up the remaining time. An outline of the topics covered over the 18 sessions can be viewed in Table 1.

**Table 1 Tab1:** CHIP sessions as per topic

Session number	Topic
1	The rise of chronic disease
2	Lifestyle as medicine
3	The common denominator of chronic disease
4	The optimal lifestyle
5	Eat more, weigh less
6	Fibre, your new best friend
7	Disarming Diabetes
8	The heart of the matter – heart healthy
9	Controlling blood pressure and discovering protein
10	Bone health essentials
11	Cancer prevention
12	Understanding your results and taking action
13	Become what you believe. Your DNA is not your destiny
14	Practicing forgiveness
15	Re-engineering your environment
16	Stress relieving strategies
17	Fix how you feel
18	From surviving to thriving

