### Statistical analysis

All data collected will be coded and entered into IBM® SPSS® version 22 for Windows® (SPSS Inc., 2013) before analysis.

#### Analysis for research question 1 and 2

Descriptive statistics will be used to analyze demographic data, anthropometric measurement data, blood results and activity levels on commencement of the program and also at the described re-evaluation intervals. Descriptive statistics will include frequencies, percentage distribution, means, and medians as well as standard deviation from the mean.

The Shapiro-Wilk test will be used to determine normal distribution to decide on whether to use parametric or non-parametric testing for correlations and variance analysis. A paired sample t-test (dependent t-test) will be used to compare pre intervention data with post intervention (12 weeks) and pre intervention data with post intervention (12 months) data. An independent t-test will be used to compare data between intervention and control groups. Pearson’s correlation will be used to explore relationships between continuous variables. The dietary inventory, health survey, and quality of life survey will be independently scored and the results between groups compared using linear regression. The level of significance is set at *p* < 0.05.

#### Analysis for research question 3

To determine the cost benefit of the intervention, a cost-benefit analysis will be undertaken. The cost benefit analysis will involve assessment of beneficial effects of the intervention. The analysis will include benefits and costs attributed to the project and indirect costs. Therefore, where B represents all the benefits and C represents all the costs, the project will be considered beneficial if B-C > 0. A cost benefit ratio will also be calculated. Costs included in the analysis will include opportunity costs. Costs from published literature and from government agencies will be used wherever possible, for example, the Medical Benefits Scheme and Pharmaceutical Benefits Scheme.

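### The independent t-test ignores that CHIP is taught in groups in one arm only, so its standard error is too small if the groups differ; ignoring the randomisation wave errs slightly the other way

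*Protocol article*

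**What the plan says.** All references are to the Protocol article.

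- **Statistical analysis (research questions 1 and 2):** "An independent t-test will be used to compare data between intervention and control groups". The dietary, health and quality-of-life scores are to be "independently scored and the results between groups compared using linear regression". Neither analysis names a term for wave or class.
- **Allocation of participants to a study group:** each wave is formed from a waiting list, in these words: "Invitees who are willing to participate will be recorded on a list until such time as there are between 30 and 40 individuals listed". Randomisation within the wave follows: "At this point, the individual participants will be randomized into either Group 1 or Group 2". The cycle then starts again: "This process will be repeated, until the full number of participants have been collected and assigned".
- **Group 1 - intervention group:** there are 18 sessions of 90 minutes. About half of each is "interactive group discussions and activities, including food preparation and exercise demonstrations delivered by CHIP trained volunteers".
- **Study setting:** CHIP is "conducted by CHIP trained volunteers in selected community halls".
- **Group 2 - control group:** usual diabetes care, with no group element.
- **Sample size estimate:** the listed assumptions are effect, allocation, dropout and standard deviation. None concerns clustering.

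**The concern.** The t-test assumes independent observations within each arm. Group 1 patients share facilitators, a hall and fellow participants over 12 weeks, and controls share nothing comparable. The design is therefore partially nested, with clustering that the intervention creates in one arm only. If some classes do better than others, 75 CHIP patients carry less information than 75 independent patients. The t-test would then report too narrow a confidence interval and too small a p-value.

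The randomisation wave is a second structural feature left out of the analysis. It has to be kept apart from class, because its effect on the standard error has the opposite sign.

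**Working it through.** **The plan's own figure.** The only relevant one is the total of 150, and it contains no clustering allowance to reproduce. Read as 3.5 units with SD 20, the stated inputs give 513 per arm and not 75. That is a separate matter, and nothing below depends on it.

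**Inputs from the article.** 150 patients, 75 per arm; lists of 30 to 40; 10% dropout.

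**Inputs assumed.** Class ICC 0.01 to 0.10. Either one or two classes per wave. Even split between arms within each wave.

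**Step 1: number of waves and class size.** 150/40 = 3.75 and 150/30 = 5, so 4 or 5 waves. Patients analysed per arm: 75 × 0.9 = 67.5.
- One class per wave: 67.5/4 ≈ 17 or 67.5/5 ≈ 13 patients per class.
- Two classes per wave: 67.5/8 ≈ 8 or 67.5/10 ≈ 7 patients per class.

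**Step 2: class effect.** With class size m, the variance of the Group 1 mean is multiplied by 1 + (m − 1) × ICC and that of the control mean by 1. Hence

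r = true SE / t-test SE = √[(2 + (m − 1) × ICC)/2].

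For m = 17 and ICC 0.10: √[(2 + 1.6)/2] = 1.342. For m = 13 and ICC 0.01: √[(2 + 0.12)/2] = 1.030.

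The approximate type I error of the nominal two-sided 5% test is 2 × [1 − Φ(1.96/r)]. For r = 1.342: 1.96/1.342 = 1.46, giving 14.4%.

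| Classes × size | ICC 0.01: r, type I | ICC 0.05: r, type I | ICC 0.10: r, type I |
|---|---|---|---|
| 4 × 17 | 1.039, 5.9% | 1.183, 9.8% | 1.342, 14.4% |
| 5 × 13 | 1.030, 5.7% | 1.140, 8.6% | 1.265, 12.1% |
| 8 × 8 | 1.017, 5.4% | 1.084, 7.1% | 1.162, 9.2% |
| 10 × 7 | 1.015, 5.3% | 1.072, 6.8% | 1.140, 8.6% |

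Simulating the plain t-test (40,000 trials per case) agrees:
- 4 × 17: 5.9%, 9.9% and 14.3%.
- 5 × 13: 5.6%, 8.8% and 12.3%.
- The two smaller-class layouts: about 5.3%, 6.8% to 7.0%, and 8.5% to 9.3%.

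At ICC 0, r = 1 and the test keeps its level.

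**Step 3: the size of the understatement.** With one class per wave, r runs from 1.030 to 1.342, so the true SE is 3% to 34% larger than the reported one. Expressed the other way, the reported SE is too small by 1 − 1/1.030 = 3% to 1 − 1/1.342 = 25%.

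**Step 4: wave effect alone.** Patients are randomised within each wave, so both arms carry the same wave effect. With an even split it cancels from the difference in means but stays in the residual standard deviation. In simulation with 75 or 76 per arm and wave ICC 0.05 to 0.10, the t-test SE was about 2% to 4% too large and type I error was 4.0% to 4.6%.

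**Step 5: both together.** With class ICC 0.05 and wave ICC 0.05, type I error was 8.8% to 10.1%. The wave effect offsets little of the class effect.

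**The case against.** Four objections deserve weight.

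1. **The size rests on figures the article does not give.** This stands. No ICC or class size is stated, and several halls could serve one wave. It is tempting to read a class of 15 to 20 off the list size, but that holds only with one class per wave. At ICC 0.01, or with smaller classes, the error is modest.
2. **Individual randomisation protects the test under the strict null.** This stands too. If CHIP affected nobody, the t-test would be approximately valid. The inflation concerns a zero average effect with class-specific effects that vary around it.
3. **A condensed article leaves modelling detail to other documents.** This is true of the form of a mixed model, and its absence is no finding. The article does, however, name the test, and that test does not fit the delivery described in the same article.
4. **With 4 or 5 classes, a random class effect is poorly estimated.** This stands. The class variance rests on 3 or 4 degrees of freedom, and nothing here shows that the mixed model holds its level exactly.

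A reader might also infer that ignoring the wave makes the p-value too optimistic. The allocation section rules this out: randomisation takes place within each wave, so the omission is mildly conservative and costs some precision.

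**Conclusion.** The point holds for class clustering in the intervention arm. The stated t-test mismatches a design with group delivery in one arm, and its standard error is too small if classes differ in their effect. The mismatch can be read directly from the article. The size cannot, and is conditional on the assumed ICC and on the class layouts in the table. Over those ranges, type I error lies between just above 5% and about 15%. It is not established that the standard error is wrong by any particular amount, since at ICC 0 it is not wrong at all.

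Leaving out the wave is a lost efficiency and not a threat to validity. The change should be made. It is inexpensive, and recruitment had not begun when the article was submitted.

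**What to change.** Replace the independent t-test, and the regression for the survey scores, with a linear model at each follow-up time. Include arm and randomisation wave as factors, plus a random CHIP-class effect in the intervention arm only, with Satterthwaite degrees of freedom. SPSS MIXED can fit this. Even with one class per wave the class effect can be separated from the wave, because that wave's controls identify the wave effect.

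Record wave for every participant and class for each Group 1 participant, and report the class ICC. Keep both variables in the coded dataset, since Ethical considerations provides for destroying the coding descriptors.

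If the class term cannot be estimated, keep wave in the model and show the result over an assumed ICC range, widening the standard error by r from the formula above. A variance estimate of zero from 4 or 5 classes should not be taken as proof of no clustering.

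The cost is some analysis wording and two recorded variables. Confidence intervals will be wider and the class variance imprecise. A test with nominal 80% power under independence would have about 65% to 67% at ICC 0.05 with one class per wave: for 75 per arm, r = 1.162 to 1.202 and power = Φ(2.80/r − 1.96), before any loss from the few degrees of freedom.

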## Methods/design

### Aims and research questions

There are two aims of this study:To assess the effectiveness of the CHIP intervention in reversing abnormal fasting blood sugar levels in people with T2DM.To determine the cost benefit of the CHIP intervention for persons with a diagnosis of T2DM.

The study will address three main questions;

In a diabetic population within a general practice group on the Central Coast of New South Wales, Australia:When compared to a control group receiving routine diabetic care, what changes occur in fasting blood sugar levels (FBSL), HBA1c, fasting lipogram with triglycerides (FLT), blood pressure (BP), abdominal girth, body mass index (BMI) and medication use among  individuals participating in the CHIP intervention delivered over a period of 12 weeks with additional monthly follow up for another 9 months?Over a 12-month period, what levels of compliance with the intervention are observed in participants?When compared to routine diabetic care, what is the cost benefit (over a 12-month period) of implementing a CHIP intervention delivered over a period of 12 weeks with an additional follow up for another 9 months?

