### Data collection

Data collection consists of a standard participant survey (including questions on food frequency, daily levels of occupational and recreational activity, smoking, hours of sleep, medical conditions and medication use), anthropometric data, blood tests, an inventory of activity, the completion of validated health, stress and diabetes quality of life surveys and cost. The costs will include cost associated with the program, monitoring and ongoing medical care. Initial data collection will occur prior to commencement of the CHIP intervention. Repeat data collection time points for both groups will be at the end of the 12-week intervention and again at 12 months from the initial commencement date.

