### Sample size estimate

The total sample required for this study is 150, with an equal number of participants in each arm of the study. The sample size was calculated on the following assumptions: a reduction in 3.5% of fasting glucose in the intervention group, an equal allocation of participants to each group as well as a 10% drop out rate. A standard deviation of 20 was used. This study is sufficiently powered d > 80% to detect a 3.5% reduction in fasting glucose using significance of 0.05 (95% confidence interval).

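### Fasting glucose is the implied main outcome, but neither the visit nor the test that decides the trial is fixed, and p < 0.05 applies to everything alike

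*Protocol article*

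**What the plan says.** Under Aims and research questions, aim 1 concerns fasting blood sugar only. Research question 1 is wider. It asks, against a control group, "what changes occur in fasting blood sugar levels (FBSL), HBA1c, fasting lipogram with triglycerides (FLT), blood pressure (BP), abdominal girth, body mass index (BMI"). The seventh item is the use of medication. All seven stand in one sentence, unranked.

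Under Data collection, both arms are measured again "at the end of the 12-week intervention and again at 12 months from the initial commencement date". The two visits have the same status.

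Under Sample size estimate, the trial is powered for a 3.5% reduction in fasting glucose "using significance of 0.05 (95% confidence interval"). The paragraph gives no visit and does not say whether the reduction is a change within the intervention arm or a difference between arms.

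Under Statistical analysis, paired t-tests compare baseline with 12 weeks and with 12 months. For the arms, "An independent t-test will be used to compare data between intervention and control groups". Further, "The dietary inventory, health survey, and quality of life survey will be independently scored and the results between groups compared using linear regression". The section then sets one level for all of these: "The level of significance is set at" p < 0.05. Fasting glucose has no special place in it.

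**The concern.** A trial's 5% error rate belongs to one defined comparison: an outcome, a visit and a test. Here the outcome can be inferred but the other two cannot. A significant paired change in the CHIP arm at 12 weeks, a between-arm difference at 12 weeks and a between-arm difference at 12 months would all meet the stated threshold, and the text does not say which counts if they disagree.

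The paired test matters most. A change from baseline within the CHIP arm does not use the randomised control group, so it cannot separate CHIP from anything else that moves glucose over a year of usual care.

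Beyond glucose, the same threshold applies to every other item at both visits. Allocation is not blinded, and the Discussion and Conclusion say the results may inform treatment decisions and funding. A reader of the results should be able to tell the deciding comparison from the rest.

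**Working it through.** **Inputs from the protocol article.** Level 0.05 for every test (Statistical analysis); seven items in research question 1; three survey instruments (Statistical analysis); two follow-up visits (Data collection).

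**Assumptions.** Tests are two-sided, since sidedness is not stated. The 11-measure count takes the lipogram as four values and blood pressure as two: glucose, HbA1c, 4 lipids, 2 pressures, girth, BMI, medication = 11. Correlations between test statistics are set at 0 to 0.5 between outcomes and 0 to 0.7 between visits. CHIP has no effect on anything.

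**Step 1: the plan's own figures.** The plan states no overall error rate. Its 0.05 is correct for one test: 1 - 0.95^1 = 0.05. The sample size does not reveal which test was meant. With a difference of 3.5 and SD 20, at two-sided 0.05 and 80% power, a between-arm comparison needs 2 x (20 x 2.80 / 3.5)^2, about 513 per arm. A paired comparison needs half that, about 257. Neither gives 75. A between-arm test reaches 150 in total, after 10% dropout, only if 3.5% is taken of a baseline mean of about 277 in the units of the SD, and the article gives no baseline mean. Failure to reproduce 150 is a separate matter; here it shows only that the deciding test cannot be worked back from it.

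**Step 2: fasting glucose alone, between arms, two visits.** If independent: 1 - 0.95^2 = 0.0975. By simulation, visit correlation 0.5 gives 0.090 and 0.7 gives 0.083. So the error is about 8-10%. Counting only results in CHIP's favour (2.5% per test), 1 - 0.975^2 = 0.049, against 0.025 for one test. Adding the paired tests in the CHIP arm raises the two-sided figure to 16-17% at visit correlations of 0.5-0.7, if glucose also does not change over time.

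**Step 3: all outcomes in research question 1, between arms, two visits.** With independent tests the chance of at least one false positive is 1 - 0.95^k in either direction and 1 - 0.975^k in CHIP's favour. Correlated cases come from simulating correlated normal test statistics.

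| Tests | Correlation (outcomes / visits) | Either direction | In CHIP's favour |
|---|---|---|---|
| 7 items x 2 = 14 | 0 / 0 | 51% | 30% |
| 14 | 0.3 / 0.6 | 43% | 22% |
| 14 | 0.5 / 0.7 | 36% | 18% |
| 11 measures x 2 = 22 | 0 / 0 | 68% | 43% |
| 22 | 0.3 / 0.6 | 57% | 30% |
| 22 | 0.5 / 0.7 | 45-46% | 23% |

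**Step 4: what the table leaves out.** Adding the three instruments, one score each (14 measures, 28 tests), gives 51-76% in either direction. Adding the paired tests in the CHIP arm to the between-arm tests gives 59-72% for seven items and 71-87% for 11 measures, over outcome correlations of 0-0.5 and visit correlations of 0.5-0.7.

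**Step 5: after the fix.** One outcome, one visit and one between-arm test give an error of 5%.

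**The case against.** The strongest reply is that fasting glucose is the main outcome in substance: it is the only clinical endpoint of aim 1 and the only basis of the power statement. That stands. It means the most direct measure of the defect is the 8-10% for glucose, not the larger figures for the whole list. It does not settle the visit or the test.

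A second reply is that a journal article condenses a fuller document, and that multiplicity methods and the reporting of secondary outcomes commonly sit in an analysis plan. For those details this is fair, and their absence is not the point. The deciding visit and comparison are different, because the sample size depends on them. The article also does more than stay silent: it states one threshold for all tests.

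A reader might infer that a false positive somewhere is likelier than not. The documents do not support that as a general statement. It fails for the seven listed items under moderate correlation, and for 11 measures at correlations of 0.5 and 0.7. The count of 11 is itself an assumption. Results that show CHIP as harmful are included in the either-direction figures; in CHIP's favour, every between-arm scenario in the table is below 50%. The figure passes 50% throughout only when paired tests or surveys are added and both directions are counted.

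A reader might also infer that the plan lets any single significant result establish effectiveness, or that the visit will be picked after seeing the data. The article says neither. It leaves the choice open.

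**Conclusion.** The point holds in this form: the implied main outcome is fasting glucose, the visit and test that decide the trial are not fixed, and 0.05 is applied equally across outcomes, visits and tests. For glucose alone, between arms at both visits, the error is about 8-10%. Across research question 1 it is about 36-51% (seven items) or 45-68% (11 assumed measures) in either direction, and about 18-30% or 23-43% in CHIP's favour. The glucose figure needs only an assumption about visit correlation. The others also depend on the assumed outcome correlations and, for 11, on how the lipogram and blood pressure are split. No scenario run for the full list comes near 5%. This should be corrected, and it is a clarification of the plan, not a flaw in the design itself.

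**What to change.** In the Statistical analysis section, name the between-arm difference in fasting glucose at one pre-specified visit as the single confirmatory test at two-sided 0.05. Twelve months fits research question 1, which describes the intervention as 12 weeks plus 9 months of follow-up. Either visit would restore the 5% error, provided it is chosen now. In the Sample size estimate, state that the 3.5% refers to that comparison at that visit. Report the other visit, the other outcomes, the surveys and all paired tests with 95% confidence intervals as supportive, without claims based on p < 0.05. A fixed testing order for a few further outcomes is an option, but nothing in the article requires one.

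The cost is about a paragraph, with the registry entry brought into line. The article says recruitment was about to begin, so at that point the change could still precede any data. The downside is weaker claims on secondary outcomes.

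### The decision rule for the cost-benefit question does not carry over the usual-care comparator and makes no allowance for sampling error

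*Protocol article*

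**What the plan says.** All references are to the protocol article.

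- **Aims and research questions.** Determining cost benefit is the second of two aims. Question 3 reads: "When compared to routine diabetic care, what is the cost benefit (over a 12-month period) of implementing a CHIP intervention". The comparator and the horizon are therefore explicit.
- **Data collection.** Cost is among the data collected: "The costs will include cost associated with the program, monitoring and ongoing medical care". On timing: "Repeat data collection time points for both groups will be at the end of the 12-week intervention and again at 12 months".
- **Statistical analysis, research question 3.** The scope is: "The analysis will include benefits and costs attributed to the project and indirect costs". The terms are defined by "where B represents all the benefits and C represents all the costs", and the verdict is that "the project will be considered beneficial if B-C > 0". A cost-benefit ratio is added. This text does not mention the control group, a difference between arms, an interval, a test or a sensitivity analysis.
- **Interventions, Group 1.** Participants who receive less than 80% of the programme content are treated as dropouts and removed from the study.

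**The concern.** The question is comparative, but the rule that answers it is not written as a comparison. Medical and medication costs can also change under usual care. If B and C were totalled for CHIP participants without subtracting the control arm, such changes would count in CHIP's favour and the randomisation would do no work for this aim.

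The rule also turns a point estimate into a verdict. Any positive value satisfies it, however small and however imprecise. This matters because the Discussion says the cost-benefit result will inform how health resources are allocated, and the Conclusion points to funded programmes. A reader told that CHIP was found beneficial could not tell a well-supported result from a coin toss.

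**Working it through.** **1. Is there a figure in the plan to reproduce?** No. No number is attached to the B-C rule. The only sample size calculation concerns fasting glucose and has no bearing here.

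**2. Comparator, section against section.**

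| Section | Comparator | Uncertainty |
|---|---|---|
| Aims, question 3 | Routine diabetic care, 12 months | Not applicable |
| Data collection | Both groups, 12 weeks and 12 months | Not applicable |
| Statistical analysis, question 3 | None stated | None stated |

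The independent t-test between groups and the paired t-test are both listed under questions 1 and 2 only. The randomised contrast in net benefit can be computed from the planned data, but the rule does not specify it.

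**3. How often the sign rule declares benefit.** This step takes the favourable reading, in which B-C is the CHIP-minus-control difference in mean net benefit per person.

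Inputs:
- 75 per arm (Study design).
- 10% dropout (Sample size estimate): 75 × 0.9 = 67.5, taken as 67 per arm.
- No cost SD is given, so the true net benefit is expressed in units of the per-person SD of net benefit.
- Assumption: an approximately normal, symmetric estimator, equal SDs and independent participants.

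Formulas:
- SE = SD × √(2/n). For n = 67, SE = 0.1728 SD. For n = 75, SE = 0.1633 SD.
- P(sign rule says beneficial) = Φ(true value / SE).
- P(lower limit of two-sided 95% interval > 0) = Φ(true value / SE − 1.96).

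Example, true value −0.1 SD and n = 67: −0.1/0.1728 = −0.579, and Φ(−0.579) = 0.28. For the interval rule, Φ(−0.579 − 1.96) = Φ(−2.539) = 0.0056.

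| True net benefit | n per arm | Sign rule | Lower 95% limit > 0 |
|---|---|---|---|
| 0 | any | 0.50 | 0.025 |
| −0.1 SD | 67 | 0.28 | 0.006 |
| −0.1 SD | 75 | 0.27 | 0.005 |
| −0.25 SD | 67 | 0.07 | 0.0003 |
| −0.25 SD | 75 | 0.06 | 0.0002 |

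**4. Precision in money, by assumption only.** The 95% half-width at 67 per arm is 1.96 × 0.1728 SD = 0.339 SD. For assumed SDs of $1,500, $3,000 and $5,000, none of which is in the document, that is about $510, $1,020 and $1,690 per person.

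**5. Who is in the calculation.** Controls attend no sessions, so the under-80% exclusion can remove people from the CHIP arm only. If it applied to question 3, the two arms would no longer be the randomised groups.

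**The case against.** **The comparator is already there.** Question 3 names routine care, data are collected in both groups, and benefits attributed to the project can fairly be read as incremental, since a change that also occurs under usual care is not attributable to CHIP. This stands in part. A reader might infer that the verdict is fixed for CHIP alone, ignoring randomisation, but the document does not say so. The rule leaves that calculation open.

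**Pre-post change.** A reader might also infer that B and C will be taken from before-after change, because a paired t-test is planned. The text does not support this: that test belongs to questions 1 and 2, and nothing ties it to B or C.

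**Non-attenders' costs.** It is tempting to conclude from the under-80% exclusion that the cost of serving people who stop attending disappears from C. The text does not settle it. C is defined as covering all costs, and total delivery cost may still be counted.

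**Programme cost.** One might compare the half-widths above with the per-person cost of CHIP, but the document gives no such cost.

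**A condensed article.** How sampling error is handled may sit in a fuller plan. That excuses the absence of method detail. It does not excuse a verdict rule that is stated here and is met by the sign of an estimate alone.

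**A sign rule can be rational, and 50% is generic.** A risk-neutral funder may act on the expected net benefit, and any sign rule with a symmetric estimator gives 50% at a true value of zero. Both points are correct. The first requires B-C to be incremental, and readers would still need its precision. The second is why the negative cases are also shown.

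**Conclusion.** The point holds in a limited form. The rule for question 3 does not carry over the usual-care comparator set in the Aims, and it makes no allowance for sampling error. The first defect is an ambiguity: a calculation without the control arm is permitted, not prescribed. The second holds on any reading. The chance of a favourable verdict is about 50% at zero true net benefit. At −0.1 SD it is about 28% with 67 per arm, against 0.6% under a 95% interval rule.

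These figures rest on a symmetric, approximately normal estimator and independent participants. Skewed costs or clustering by class would change them somewhat. The dollar half-widths are only as good as the assumed SDs. The rule should be changed because it decides one of the trial's two aims, but the change is one of definition and reporting, not of design.

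**What to change.** Replace the B-C > 0 sentence with a definition and a reporting rule:

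- **Estimand.** Incremental net benefit: the mean of benefit minus cost per person over 12 months in the CHIP group, minus the same mean in the control group.
- **Population.** All randomised participants, whatever their attendance. State that the under-80% exclusion does not apply to this analysis.
- **Uncertainty.** A bootstrap 95% interval, resampling participants within arm, and the probability that incremental net benefit exceeds zero. If clustering is to be reflected, resample whole CHIP classes across waves. Resampling classes within a wave should be avoided: lists of 30 to 40 give about 15 to 20 CHIP participants per wave, possibly a single class, and resampling one class adds no between-class variation. With 150 people there are only about 4 to 5 waves (150/40 = 3.75; 150/30 = 5), so a class-level interval would itself be rough.
- **Conclusion.** Base it on the estimate and its uncertainty, with the cost-benefit ratio as secondary.

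The cost is revised wording and some programming. Cost is already among the planned data, with repeat collection in both groups, and the Study status section says recruitment had yet to begin. The downside is that the verdict may be less clear-cut.
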